### Research Proposal

impact of stopping statin monotherapy and the rechallenge of statin monotherapy under vitamin D repletion. As described in objective #1, and for both groups, muscle strength and fatigability tests and venous punctures (particularly for 25-OH vitamin D level assessments) will be obtained immediately prior to statin reintroduction (after one month of vitamin D or placebo). These and muscle biopsies will also be taken at the end of the statin-reintroduction period (within 1 week of the maximum 2 months trial length or from when patients cease statin use due to reappearance of important MRSE).

Muscle biopsies of the *vastus lateralis* will be obtained for 30 of these patients: 10 presenting MRSE and receiving vitamin D, 10 presenting MRSE and not receiving vitamin D, 5 without MRSE and receiving vitamin D, and 5 without MRSE and not receiving vitamin D. These will be the same patients that had biopsies in objective #1, allowing us to evaluate changes to skeletal muscle tissue over time. Our laboratory has extensive experience in multiple biopsies from the same patient over time, and we have published numerous papers using this approach (e.g., [49, 53-57]).

In addition to the testing and questionnaires outlined in Figure 1, phone interviews will be performed every 2 weeks during the RCT to assess adverse events. An adverse event is any untoward medical occurrence in a study subject that is temporally associated with the use of a medicinal product, regardless of its potential relationship to the medicinal product. An adverse event, therefore, can be any unfavorable or unintended sign, symptom or disease (new or exacerbated), whether or not related to the study drug. The severity of an adverse event will be scored according to the following scale:

Mild: Awareness of sign or symptom, but easily tolerated

Moderate: Discomfort enough to cause interference with usual activity

Severe: Incapacitating with inability to perform usual activities

Participants will be provided with the adverse event guide presented in **Appendix 3** to help classify the nature and intensity of adverse events during phone interviews and in questionnaires.

Participants will be required to provide informed consent, will be assured confidentiality and will be offered the possibility to withdraw from the study at any time and without justification. Premature withdrawals and their causes will be carefully documented. Subjects who withdraw before the required sample size has been attained will be replaced; those who withdraw after the required sample size has been attained will not be replaced.

**EXPECTED FINDINGS AND OUTCOMES.** *This second phase of the proposal will allow us to confirm that MRSE suffering patients may be protected against statin-induced myalgia as well as for muscle function and biological markers of muscle cell degeneration after vitamin D supplementation. In addition, these data will demonstrate a significantly improved capacity to achieve lower LDL-cholesterol levels in cardiovascular prevention while reducing the risk of muscle side-effects from statin use.*

Primary outcomes for this objective include: (1) reduced functional impact of statins on muscle strength and endurance in the vitamin D supplemented group, and (2) a greater tolerance of statin reintroduction (i.e., fewer self-reported MRSE) in the group receiving vitamin D supplementation; secondary outcomes will be (3) the normalization of muscle histological, ultrastructural, and mitochondrial (metabolic) abnormalities with vitamin D supplementation and (4) the demonstration of improved statin tolerance with vitamin D supplementation regardless of initial 25(OH)D status.

#### 4.0 Clinical follow-up and safety concerns

**Clinical and anthropometric measures.** In addition to medical history, traditional blood work (glycemia, insulinemia, lipid-lipoprotein profiles...) as well as anthropometric measurements (body weight, height, waist circumference...) will be obtained for all patients over the course of the study. Other specific analyses are presented in the appropriate sections that follow.

---

**Research Proposal**

---

**Statin efficacy.** The percent change in serum total cholesterol, LDL-cholesterol, apolipoprotein B, HDL-cholesterol, apolipoprotein A-1 and triglycerides, from baseline to end of each phase of study will be studied in all patients to evaluate the impact of discontinuation of statin therapy and the rechallenge of statin monotherapy under vitamin D repletion on cardiovascular risk factors.

**Questionnaires (see APPENDIX 3 for all questionnaires).** The PIQ6 Pain impact questionnaire will be used to assess the perceived impact of MRSE on everyday activities. Perceived general health will be assessed using the SF-12v2 Health Survey Scoring questionnaire. An in house questionnaire will be used to evaluate the nature and perceived intensity of MRSE. This questionnaire will also explore aspects of medical history (such as recent illness, other potentially related diseases, family history of pain) that could impact MRSE. Three versions of this questionnaire will be used: one to evaluate subjects in the screening and pre-withdrawal phase, a second following 2 months of statin withdrawal, and a third at the end of the statin reintroduction period in the vitamin D randomized placebo controlled trial.

**Adverse events and other serious events.** Participants will immediately be withdrawn from the trial should any change in their health occur over the course of the study that warrants immediate medical care using standard medical guidelines.

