**Hypotheses:** 1) Patients under statin monotherapy and suffering from statin-induced MRSE show reduced muscle strength and increased fatigability associated with an increased prevalence of cell damage, proteolytic markers, and perturbed mitochondria. 2) The cessation of statin monotherapy improves muscle function and reduces biological markers of muscle cell degeneration in patients with MRSE. 3) Vitamin D supplementation followed by statin reintroduction protects against statin-induced MRSE.

**Patient population:** Men and women aged between 30-60 years (inclusive) and affiliated with the cardiovascular prevention lipid clinic at the Laval University Hospital Research Centre (CHUL) will be included in this study. Patients treated with statin therapy for the first time in the last year with or without MRSE and with normal creatine kinase (CK) blood levels will be recruited. These patients must not have taken statins or lipid-lowering drugs before the last year or consume vitamin D supplements. MRSE must clearly have begun after statin introduction. These patients will be in low cardiovascular risk primary prevention, allowing us to modify their lipid-lowering drug regimen for a short period of time.

**Impact:** A better understanding of the cellular and molecular events leading to muscle pain, damage and dysfunction in the presence of statins is essential for the design of effective therapeutic modalities. We are convinced that this project will provide the basic foundation for this and may position Canada as a world leader on how to deal with MRSE associated with statins. Lastly, the present proposal also proposes an alternative treatment by testing the combination of statins and vitamin D supplementation to alleviate MRSE, an area in which clinical research and transferable solutions to patients are crucially needed.

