**Vitamin D deficiency and myalgia.** Vitamin D deficiency is highly prevalent worldwide and low serum levels of 25-hydroxyvitamin D (25(OH)D) are associated with higher risk of cardiovascular morbidity and mortality [25]. Vitamin D deficiency is also associated with a number of muscle symptoms, *e.g.*, myalgia strikingly similar to that resulting from statins [26], and has also been associated with myositis [27]. Vitamin D insufficiency is highly prevalent in patients with type 2 diabetes and may cause neuropathic pain in the inadequate (serum 25(OH)D levels of 40–60 nmol/l) rather than severely deficient range (25(OH)D <30 nmol/l) [28].

**Vitamin D and muscle morphology and performance.** Effects of vitamin D levels on muscle performance have been reported in a few studies, vitamin D possibly improving muscle strength and function through a highly specific nuclear receptor in muscle tissue. Studies showing associations between vitamin D status and physical performance walking speed, sit-to-stand times, handgrip strength,

---

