**Trial design**

This study will use an outpatient, randomized, double-blind (participants, research nurse, coordinator, investigators, interviewers, statisticians, treating physicians), prospective trial design with stratification on MRSE status, plasma 25(OH)D status, age and sex, with repeated measures at 4 weeks post-randomization and at up to 8 weeks post-statin reintroduction. This is diagrammed in Figure 1. Participants (from Objective #1) will first be divided into 2 groups according to their MRSE status: statin taking with MRSE and statin taking without MRSE. Participants in each group will then be randomly assigned to either the experimental (vitamin D) or the control (placebo) arm. The placebo will as closely as possible match the color, taste and consistency to the vitamin D administered in the experimental group.

The research coordinator and other members of the research team will be responsible for recruitment, testing, data collection and follow-up. Allocation of participants to treatment arms and statin, vitamin D and placebo supply and distribution will be under the responsibility of the Department of Pharmacy of the CHUL (see budget supporting document).

Vitamin D status will not be used to select subjects for initial (Objective #1) enrolment in the study, but will be used to stratify subjects in the RCT. Subject vitamin D status will be defined using cut-offs discussed in a recent Statistics Canada Health Report [45].

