In the experimental group (n=45; 30 with MRSE under statin monotherapy, 15 without MRSE under statin monotherapy from objective #1), statins will be reintroduced following one month of oral vitamin D supplementation (Vitamin D3 [cholecalciferol], Laboratoire Riva Inc., Blainville, Québec; 4 x 10,000 IU/week, 40,000 IU/week total). This falls within the range of average daily dosage used in the studies of Lee *et al.* [44] and Ahmed *et al.* [43] that showed relief from myalgia and allowed statin reintroduction in patients with low serum 25(OH)D levels. This also falls within the generally acceptable upper limit of daily vitamin D intake, the “no observed adverse event level” being 10,000 IU per day, and well below the “lowest observed adverse event level” of 40,000 IU per day (as discussed in [45]). Patients will be rechallenged with the same statin and at the same dose they were taking at the onset of objective #1. Patients will continue to supplement with vitamin D during the statin rechallenge period, which will last for a maximum of 2 months. The patients may request at any time over this period the cessation of statin therapy if they consider any reappearance of MRSE to be too severe to continue. Based on the clinical experience of [name] (co-PI), patients rarely develop muscle symptoms in less than 2 weeks following statin introduction.

In the control group (n=45; 30 with MRSE under statin monotherapy, 15 without MRSE from objective #1), no vitamin D supplementation will take place prior to statin reintroduction, subjects receiving instead a placebo provided by the pharmacy service of the CHUL. Placebo supplementation will also continue following statin reintroduction (1 month after the start of the RCT). Readers are referred to figure 1 and table 1 for more details on patient assignment.

Participants will be asked by the study coordinator, by phone, a few days before their visits at 4 weeks after randomization and at end-of-trial, to bring their bottles of capsules for their visit to the CHUL. The pharmacy will then check their apparent compliance by counting the remaining capsules and surveying the participants on their supplementation practices. A compliance rate of at least 80% will be required for successful outcome in the trial.

The changes in 25-OH vitamin D, calcium, phosphate, alkaline phosphatase, and parathyroid hormone, from baseline to end of each phase of study will be studied in all patients to evaluate the

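### The in-house muscle-symptom questionnaire is not timed between the month of capsules and statin restart, so the end-of-trial symptom difference cannot separate relief of background pain from protection against the statin

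*Protocol*

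**What the plan says.** **Symptom readings.** Section 4.0 (Questionnaires) assigns three versions of the in-house MRSE form. The first belongs to screening and the time before statin is withdrawn. The other two are timed as follows: "a second following 2 months of statin withdrawal, and a third at the end of the statin reintroduction period". The section names PIQ6 and SF-12v2 without giving times for them.

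**Sequence in the randomised phase.** Under Objective #2, Trial design, "statins will be reintroduced following one month of oral vitamin D supplementation", and capsules continue during rechallenge. The design is described as "with repeated measures at 4 weeks post-randomization and at up to 8 weeks post-statin reintroduction", without naming instruments. For the visit after the month of capsules, the text says that "muscle strength and fatigability tests and venous punctures (particularly for 25-OH vitamin D level assessments) will be obtained immediately prior to statin reintroduction". No questionnaire is mentioned there. The same section refers to Figure 1 for the schedule of tests and questionnaires.

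**The claim.** Hypothesis 3 in section 1.0 reads: "Vitamin D supplementation followed by statin reintroduction protects against statin-induced MRSE". Primary outcome (2) of Objective #2 treats a lower count of self-reported MRSE in the vitamin D arm as better tolerance of the reintroduced statin.

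**Background.** Section 2.0 says that vitamin D deficiency is associated with "myalgia strikingly similar to that resulting from statins".

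**The concern.** Vitamin D could lower the end-of-trial symptom score in two ways. It could ease muscle pain that is present whether or not the patient takes a statin, or it could prevent pain that the statin brings back. Hypothesis 3 concerns only the second. Both are effects of the randomised treatment, so randomisation and stratification on 25(OH)D balance the arms but do not separate them. Every randomised patient is due to be rechallenged, so no arm shows vitamin D without statin at the end of the trial.

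A reading after the capsules have acted and before the statin returns would help to separate the two. Strength and endurance have that reading. On the text, the in-house MRSE form, which supports the symptom primary outcome, does not. The reading cannot be recovered once a patient has restarted statin.

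**Working it through.** **1. Assessments in order, from the text alone**

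| Time | In-house MRSE form | Function tests | Blood |
|---|---|---|---|
| On statin, before withdrawal | version 1 | yes | yes |
| 2 months off statin, before capsules | version 2 | yes | yes |
| After 1 month of capsules, before statin restarts | none timed | yes | yes |
| End of reintroduction (at most 2 months) | version 3 | yes | yes |

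The last timed MRSE reading before the end comes before the first capsule. An end-minus-baseline change (section 5.0) therefore contains both effects whichever earlier MRSE reading serves as baseline. The two-weekly phone calls record adverse events, defined as new or worsened complaints, so they do not capture relief of existing pain.

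**2. Size of the ambiguity**

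The plan states no figure to reproduce. The following is an illustration in which vitamin D gives no protection at all against the statin.

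Inputs from the protocol: 30 MRSE patients per arm; two-sided alpha 0.05.

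Assumptions, not in the documents:
- The outcome is any MRSE at the end, yes or no.
- Background pain and statin recurrence are independent.
- The share whose symptoms recur on statin is r = 0.3 to 0.7.
- The share with residual pain off statin is b = 0 to 0.4.
- The share of that residual pain relieved by vitamin D is e = 0.5 to 1.

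Formulas:
- Placebo: p₀ = 1 − (1 − r)(1 − b)
- Vitamin D: p₁ = 1 − (1 − r)(1 − b(1 − e))
- Spurious difference: p₀ − p₁ = (1 − r)·b·e
- Chance of significance in favour of vitamin D: Φ[(p₀ − p₁ − 1.96·SE₀)/SE₁], where SE₀ is the pooled and SE₁ the unpooled standard error with n = 30 per arm.

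Worked case, r = 0.3, b = 0.2, e = 1:
- p₀ = 1 − 0.7 × 0.8 = 0.44 and p₁ = 1 − 0.7 × 1 = 0.30, a difference of 0.14.
- The pooled proportion is 0.37, so SE₀ = √(2 × 0.37 × 0.63/30) = 0.1247.
- SE₁ = √((0.44 × 0.56 + 0.30 × 0.70)/30) = 0.1233.
- Φ[(0.14 − 1.96 × 0.1247)/0.1233] = 0.199, about 20%.

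Over the grid of r and e:

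| Residual pain off statin, b | Spurious difference | Chance of a significant result favouring vitamin D |
|---|---|---|
| 0 | 0 | 2.5% (nominal) |
| 0.1 | 1.5 to 7 points | about 3% to 8% |
| 0.2 | 3 to 14 points | about 5% to 20% |
| 0.4 | 6 to 28 points | about 8% to 59% |

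The 59% is the extreme corner: low recurrence (r = 0.3), high residual pain and complete relief.

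**3. What a week-4 reading would and would not settle**

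The change from week 4 to the end removes the background effect that is complete by week 4. Capsules continue during rechallenge, and one repletion study cited in section 2.0 ran for 12 weeks, so some effect may build later. Suppose, as an assumption, that half of a 0.6 SD background effect came after week 4 and change scores had SD 1. A 0.3 SD shift would then remain, and a two-sample t test at 30 v 30 would detect it about 21% of the time. The reading reduces the ambiguity and need not remove it.

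**The case against.** **The schedule may be in Figure 1.** The legend places Q1 to Q3 on the timeline, Objective #2 refers to the figure, and repeated measures at 4 weeks are promised without naming instruments. A reader might infer that no symptom questionnaire of any kind is given at week 4. The text does not support that: PIQ6 and SF-12v2 may be there. Section 4.0 also describes versions and may not list every administration. What stands is that no version of the in-house form is assigned to week 4. If Figure 1 shows one there, section 4.0 needs to say so.

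**Residual pain may be small.** MRSE must have begun after statin was started. Many painful conditions are excluded, as is 25(OH)D below 12.5 nmol/L. All nine pilot patients reported important falls in pain after withdrawal, and version 2 measures residual pain just before capsules. A reader might infer that vitamin D's relief of ordinary pain will be reported as protection. That goes too far: the two effects cannot be told apart, and the mixture may be slight.

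**The background evidence is limited.** A reader might take section 2.0 to say that low vitamin D causes the same pain. It reports an association. The 64% with low 25(OH)D among myalgic statin users stands beside 43% among asymptomatic users; both groups were on statins, so neither figure shows non-statin pain.

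**The randomised comparison answers the objective.** Objective #2 asks whether vitamin D is useful in reducing muscle side effects, and the total effect addresses that. This stands. Only attributing the difference to protection against the statin lacks support.

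**Conclusion.** The point holds in a limited form. On the text shown, the in-house MRSE form is not timed at the visit after one month of capsules and before statin restarts, where function and blood are measured. The end-of-trial arm difference in self-reported MRSE is a valid estimate of vitamin D's total effect. Alone, it cannot establish Hypothesis 3 or the tolerance reading of primary outcome (2). The strength and endurance outcome is not affected.

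The bias runs from none to substantial, depending on residual pain off statin, and the percentages above rest on assumed rates. They show when the gap would matter and do not forecast the trial's error. Because the missing reading is cheap to take and cannot be obtained later, the change should be made.

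**What to change.** 1. In section 4.0 and in Objective #2, Trial design, add the in-house MRSE questionnaire at the existing 4-week visit, before statin restarts, with the same symptom items as at the end. Add PIQ6 there if Figure 1 does not already place it. Make the text and Figure 1 agree.
2. Keep the randomised end-of-trial comparison as the primary symptom analysis.
3. Beside it, report the arm difference at week 4 (vitamin D without statin) and the arm difference in change from week 4 to the end of rechallenge.
4. Word any claim of protection against statin-induced MRSE in the light of both, noting that vitamin D's background effect may continue to build after week 4.

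Cost: a few minutes per patient at a visit that already takes place, and a short protocol edit.

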## **5.0 STATISTICAL ANALYSES**

Although there are no published data on the loss of muscle force in humans following statin treatment, experiments using men with coronary artery disease showed that  $n = 10$  to  $20$  is sufficient to distinguish differences between groups [58]. Based on the high accuracy of the Biodex apparatus and our preliminary data, we calculate that a total of 60 MRSE suffering patients will be sufficient to demonstrate effects on muscle function by statin withdrawal or vitamin D supplementation (30 per group, one with vitamin D, the other with placebo - see APPENDIX 3 for Power Calculations). These sample sizes are similar to those producing data showing reversible myositis-myalgia in statin-treated low serum 25(OH)D patients receiving vitamin D repletion [43, 44]. For biopsies, the number of subjects in each study group was determined based on our previous work (*e.g.*, [49]), biopsy feasibility and the availability of patients from our clinic [59]. From the patient case reports documented with some of these MRSE and considering the analytical precision of the methods proposed, we are confident that we will show statistically significant differences between MRSE suffering and not suffering patients [13].

Statistical analyses will test the comparison of subgroups (with/without symptoms and with/without vitamin D repletion) on the percent change from baseline (end – baseline) of specific measurements. Changes from baseline (end – baseline) of all clinical muscle symptoms will be also analyzed. Normal distribution of fasting marker levels will be examined and, if necessary, they will be normalized by transformation prior to statistical analyses in order to reduce the skewness of their distribution. One-way ANOVA will be used to compare means of continuous variables. Differences in proportions (*e.g.* proportion of patients having increments in one or more specific markers) will be compared using either the Chi-square test, or the Fisher's exact test when appropriate. Statistical analyses will be performed using SAS (SAS Institute Inc.) and/or JMP (SAS Institute Inc.) software. All tests will be two-tailed and considered statistically significant when alpha level  $< 0.05$ .

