The first study to examine the possible associations of statins and muscle strength was that of Phillips *et al.* [13]. Hip flexion and abduction strength was measured in 4 patients with muscle myopathy, but with normal creatine kinase and statin blood levels. Compared to measures while off statins, statin use by these patients resulted in ~25% and ~19% decreases in hip flexion and abduction strength, respectively.

Using data from the Tasmanian Older Adults Cohort Study (TASOAC), Scott *et al.* [7] reported that statin users aged 50-79 years had significantly lower mean leg strength (isometric muscle strength of the quadriceps and hip extensors assessed with a dynamometer) than non-users. Over time, statin users also lost more strength and muscle mass compared to those who had stopped statin therapy after first entering the prospective study. These data suggest that statin use reversibly decreases muscle strength in older adults. In the observational Hertfordshire Cohort Study, no effect of statins on handgrip strength was noted in a group of men and women aged 59-73 [14]. In both of these studies no distinction was made between statin users with or without MRSE.

In terms of exercise capacity, data from published studies appear to be contradictory. A prospective study on the effects of 12 weeks of high-dose statin therapy (simvastatin 80 mg/day) in 10 patients aged 55-76 yrs failed to show any change in aerobic capacity, endurance, oxygen kinetics or muscle strength (chest press and leg press 1-RM) [15]. None of the subjects in this study reported symptoms of myalgia or cramps, leading the authors to conclude that in the absence of myalgia or myopathic symptoms, high-dose simvastatin treatment did not impair exercise capacity in hyperlipidemic older individuals.

In patients with stable congestive heart failure, atorvastatin treatment for 8 weeks improved flow-dependent brachial vasodilation and increased average 6 min walking distance by about 10% [16]. In patients with peripheral arterial disease, atorvastatin [17] and simvastatin [18] improved pain-free walk time when compared to placebo, presumably by improving the endothelial vasodilatory response to exercise. A recent meta-analysis [19] concludes that statins are the most efficient pharmacotherapy to improve mean walking distance in patients with intermittent claudication caused by peripheral vascular disease. Again, no information on MRSE status of the patients in these studies is available.

---

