Following screening, 60 patients presenting MRSE (assessed by a standardized questionnaire; see **Appendix 3, questionnaire 3**) under statin monotherapy (any statin, any dosage) as well as 30 patients without MRSE under statin monotherapy (paired for statin and dosage with the MRSE cohort) will be evaluated. Muscle strength and fatigability will be tested by standardized procedures before and after two months of stopping statin monotherapy. Briefly, strength of the extensors and flexors muscles of the dominant leg will be quantified with a Biodex isokinetic dynamometer available in our research centre. Forces will be tested during 3 reps at 60 and 180 deg/sec and endurance during a 15 reps test at 180 deg/sec. These tests will be preceded by a 5 reps warm-up at 60 deg/sec including one movement at maximal voluntary contraction [46]. Each maximal concentric contraction will be performed in the first 90 degrees of the knee range of motion. Patients will sit in an upright position and mechanical axis and resistance pads will be aligned according to the manufacturer's guidelines. The results will be reported in Newton-meters (Nm). Peak torque, rate of torque development and total work values will be obtained following these isometric and isokinetic measurements. These groups of muscles were selected because muscle weakness or myalgias with statins are most frequently localized in lower limbs. Handgrip strength of the dominant hand will also be tested in a static mode with a Jamar dynamometer (best of 3 repetitions). These testing procedures are well standardized, easy to perform and very reproducible, and are routinely used in the department of physical therapy at our centre. Test-retest variability for the Biodex measurements is shown to be within  $\pm 15\%$  [46], which our personal experience confirms. The primary efficacy parameter will be the percent change for these measurements from baseline to end of each phase of the study.

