**Research Proposal**

---

Subjects (see **APPENDIX 1, Table 1**) in our study were statin users and had muscle side effects (cramps, myalgia, reduced muscle endurance) evaluated with our in-house questionnaire (see **APPENDIX 3, questionnaire 3**). All subjects were in primary cardiovascular prevention. Different statins were used by different participants, the majority at low doses (the highest being 20 mg).

After statin withdrawal, all subjects reported important decreases in the level of pain experienced (**APPENDIX 1, Figure 1**), and 70% showed functional improvements in at least one Biodex measure of muscle performance (**APPENDIX 1, Figure 2**). On average, the strength of the extensor and flexor muscles increased by  $22\pm 43\%$  and  $17\pm 28\%$  respectively, power by  $28\pm 64\%$  and  $29\pm 41\%$ , and endurance by  $28\pm 57\%$  and  $20\pm 35\%$  (means $\pm$ SD). No effects were observed on blood CK and AST values (**APPENDIX 1, Table 2**).

Our preliminary results show that cessation of statin therapy increased muscle functional capacity in the majority of subjects who experienced *a priori* muscle discomfort. ***Since this condition could affect the pharmacological compliance and potentially modify the cardiovascular benefits of statins, it is imperative to better characterize this dysfunction and develop approaches to reduce its impact.***

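### The preliminary data support 60 MRSE patients for the withdrawal effect, but do not support 30 per arm as sufficient for vitamin D versus placebo on muscle function

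*Protocol*

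**What the plan says.** Protocol section 5.0 claims that "a total of 60 MRSE suffering patients will be sufficient to demonstrate effects on muscle function by statin withdrawal or vitamin D supplementation", divided as "30 per group, one with vitamin D, the other with placebo". The stated basis is "Based on the high accuracy of the Biodex apparatus and our preliminary data". It adds that the sizes resemble those of earlier vitamin D repletion reports, which section 2.0 describes as uncontrolled, with 38 supplemented and 6 rechallenged patients.

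The preliminary data are in section 3.0, Objective #1. Nine patients with MRSE were tested on statin and again 2 to 3 months after stopping. "On average, the strength of the extensor and flexor muscles increased by" 22±43% and 17±28%; power rose by 28±64% and 29±41%, and endurance by 28±57% and 20±35% (extensor, then flexor; mean±SD).

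On the endpoint, "The primary efficacy parameter will be the percent change for these measurements from baseline to end of each phase of the study". Section 5.0 compares subgroups, including with and without vitamin D, on percent change. It also says: "All tests will be two-tailed and considered statistically significant when alpha level" is below 0.05. Objective #2 lists a smaller functional impact of statins on strength and endurance under vitamin D as a primary outcome, next to statin tolerance.

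The body gives no target difference, planning SD or power. It refers to Appendix 2 in section 3.0 and to Appendix 3 in section 5.0 for the calculation; neither is in the supplied text.

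**The concern.** The withdrawal question is a within-patient change in all 60 MRSE patients. The vitamin D question is a difference between two arms of 30. On the same mean and SD, the noncentrality of the second is half that of the first, so data that comfortably support one need not support the other.

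Device accuracy does not close the gap. The figure of ±15% in section 3.0 is test-retest variability. A two-arm test of percent change faces the spread of change between patients, which the protocol's own data put at 28 to 64%. The earlier repletion series report symptom resolution and tolerance without a control group, so they do not inform a two-arm functional comparison.

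At stake is how a non-significant functional result in the randomised phase would be read. If the protocol calls the size sufficient, such a result invites the conclusion that vitamin D does not protect muscle, when the trial may have had modest power to show it.

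**Working it through.** **Plan's own figure.** The only stated figure is 60 in total, 30 per arm. With no difference, SD or power beside it, it cannot be reproduced directly. Working back from the preliminary data with an assumed 80% power (normal approximation), n per arm = 2(1.960+0.842)²(SD/Δ)² = 15.70(SD/Δ)². For extensor strength this is 15.70×(43/22)² = 60. Across the measures, in the order of the table, it is 60, 43, 83, 32, 66 and 49. Only flexor power comes near 30.

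**Inputs.** Δ and SD: the six means and SDs in section 3.0. Alpha: two-sided 0.05. Arms: 30 and 30. Assumptions: vitamin D abolishes the whole mean effect, the change on rechallenge has the same size and SD as the change on withdrawal, SDs are equal, and nobody drops out.

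**Formulas (noncentral t).**
- Two arms: ncp = Δ/(SD×√(2/30)), 58 df. Extensor strength: 22/(43×0.2582) = 1.98, power 50%.
- Half protection: the same with Δ/2.
- Difference detectable with 80% power: 0.736×SD. Extensor strength: 0.736×43 = 31.6 points.
- Paired withdrawal: ncp = Δ√60/SD, 59 df. Extensor strength: 22×7.746/43 = 3.96, power 97%.

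| Measure | Mean±SD (%) | 30 v 30, full | 30 v 30, half | Detectable at 80% (points) | Detectable ÷ mean | Paired, n=60 |
|---|---|---|---|---|---|---|
| Extensor strength | 22±43 | 50% | 16% | 31.6 | 1.44 | 97% |
| Flexor strength | 17±28 | 64% | 21% | 20.6 | 1.21 | >99% |
| Extensor power | 28±64 | 38% | 13% | 47.1 | 1.68 | 91.5% |
| Flexor power | 29±41 | 77% | 27% | 30.2 | 1.04 | >99% |
| Extensor endurance | 28±57 | 46% | 16% | 41.9 | 1.50 | 96% |
| Flexor endurance | 20±35 | 59% | 19% | 25.7 | 1.29 | 99% |

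**Sensitivity.**
- *Smaller SD in the vitamin D arm.* If it were 15% (an assumption that reads the test-retest figure as an SD), Welch power at full protection is 73, 82, 62, 94, 71 and 80%, in table order.
- *Imprecise SDs.* With 8 df the 95% limits of an SD are 0.68 and 1.92 times the estimate. At the lower limits 30 v 30 gives 69 to 98%. At the upper limits even the paired test in 60 falls to 41 to 80%.
- *Dropout.* At 24 per arm (20% loss, an assumption) power at full protection is 32 to 67%.
- *Preliminary effects.* t = mean/(SD/√9) gives 1.53, 1.82, 1.31, 2.12, 1.47 and 1.71 on 8 df, p = 0.07 to 0.23. None differs from zero at 5%.

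**The case against.** The strongest reply is that the actual calculation is in an appendix that is not supplied. It may use another measure, difference, SD or power target, and 80% is my benchmark, not the plan's. That stands. A reader might infer that the appendix is miscalculated, or that the planners used 15% as the SD. The documents show neither. What can be said is that the preliminary data named as the basis do not deliver the claim for vitamin D.

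Second, a reader might take 38 to 77% as a ceiling and conclude that the trial could not detect even full protection. That goes too far. Complete protection would probably also remove variation in statin response from the vitamin D arm, and with an SD of 15% there power is 62 to 94%. Even with equal SDs, 64% and 77% are far from nil.

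Third, SDs from 9 patients are imprecise. This is true and cuts both ways, including for the withdrawal claim. It argues for stating the assumptions, not for an unqualified assertion of sufficiency.

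Fourth, statin tolerance is also a primary outcome of Objective #2, so the randomised phase does not rest on function alone, and reporting conventions may sit in an analysis plan. That lowers the weight of the point. The sufficiency claim itself is nevertheless made in the protocol, so this is a statement to correct and not an omission.

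**Conclusion.** The point holds for the vitamin D comparison only. On the preliminary data, 60 patients are adequate for the paired withdrawal change (91.5% to over 99%). Thirty per arm gives 38 to 77% for complete protection, 46 to 64% on the strength and endurance measures named as a primary outcome, and 13 to 27% for half protection. The difference detectable with 80% power is 0.74 SD, which on every measure exceeds the whole mean withdrawal effect (1.04 to 1.68 times). This assumes equal SDs, a rechallenge effect that matches the withdrawal effect, no dropout, and SDs estimated from 9 patients.

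Separately, and with no bearing on power, section 5.0 says "Although there are no published data on the loss of muscle force in humans following statin treatment", while section 2.0 reports that in one earlier study of 4 patients "statin use by these patients resulted in ~25% and ~19% decreases in hip flexion and abduction strength". The two should be made to agree.

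**What to change.** In section 5.0:

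1. Separate the two comparisons and keep the sufficiency claim for the withdrawal change only.
2. For vitamin D versus placebo, replace that claim with the power and the detectable difference at 30 per arm for each measure. State the assumed difference and SD, and say that the SDs come from 9 patients.
3. Do not cite test-retest accuracy or the uncontrolled series of 38 and 6 patients as support for the two-arm functional comparison.
4. Report the functional result of the randomised phase as an estimate with a 95% confidence interval, and state that a non-significant result is not evidence of no protection.
5. Reword the clause on absent published data to agree with section 2.0. Do not delete the sentence, because it also carries the reference to group sizes of 10 to 20, which cannot be assessed here.

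The cost is wording and a less favourable stated power. No extra patients, procedures or endpoints are needed.
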